#### Efficacy

The primary analysis will follow the intention-to-treat (ITT) principle. The primary outcome survival will be analyzed by a Cox proportional hazards regression. The treatment effect will be reported as hazard ratio with 95% confidence intervals and p-value testing the null hypothesis of no effect (i.e. a hazard ratio of 1). Patients withdrawing from study treatment will be followed up for endpoints. Withdrawal from the study will be dealt with as independent right censoring in the primary analysis unless the patient’s vital status can be obtained at end of study. If withdrawal from study is substantial and differential between the treatment groups, supporting analyses will explore the impact of the independent right censoring assumption by use of shared frailty models for time to death and time to withdrawal from study.

The analyses of the time-to-event outcomes among the secondary endpoints will follow the same lines as the analyses of the primary endpoint. Quality of life (EORTC QLQ-C30, PAN-26, CIPN20, Q-TWIST) and continuous outcomes assessed repeatedly will be analysed using the so-called Mixed Model Repeated Measures (MMRM) approach. Treatment differences will be reported as least square means with 95% confidence intervals.

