### Endpoints

The primary endpoint is overall survival (OS) as the time from randomization to death of any cause. Secondary endpoints include progression-free survival (PFS), quality of life (EORTC QLQ-C30, PAN-26, Q-TWIST) and translational endpoints. PFS is defined as the time from randomization to death or progression whatever occurs first. During the induction phase of the study, response will be assessed according to RECIST v1.1. Progression is based on radiological assessment according to RECIST v1.1.

For translational research purposes, tissue from the initial diagnostic biopsy and the resection specimen will be collected, if possible from both tumor tissue from the primary tumor and from metastases (this should be feasible at least for patients that were surgically explored). Aims are to identify predisposing factors for metastasis, response to mFOLFIRINOX treatment and adaptive molecular changes under chemotherapy. Characterization will address the molecular subtype and clonal evolution to better understand mechanisms of metastasis and to identify chemotherapy response / resistance patterns.

Blood samples are taken before each chemotherapeutic cycle, before surgical resection and during maintenance therapy and surveillance. Analysis will focus on circulating tumor DNA, analysis for monitoring of mutational patterns of pancreatic cancer during cancer therapy (prognostic for disease survival, predictive for primary or secondary drug resistance) in comparison to currently used tumor markers (CA19- 9) using e.g. a multiplex amplicon-based sequencing approach (Table 1).

**Table 1 Tab1:** Objectives and endpoints of the METAPANC trial

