### Statistical considerations

#### Sample size calculation

The sample size calculation is driven by the primary endpoint overall survival. Recruitment will be over 5 years and all patients will be followed up for at least 2 additional years, unless the patient dies beforehand, resulting in a maximum follow-up of 7 years. Assuming two-year survival probabilities of 15% in the control arm [1] Fig. 1A mFOLFIRINOX arm) and 30% in the experimental arm a sample size of 109 patients per group will yield a power of 90% at the usual two-sided significance level of 5%. The assumed two-year survival probability of 30% in the experimental treatment arm corresponds to a hazard ratio of 0.635, which is considered clinically relevant. Adjusting conservatively for about 20% dropout (i.e. study discontinuations following randomization) we aim to randomize a total of 272 patients. The sample size calculation was carried out using nQuery (version 8.2.0.0). Assuming that about two thirds of the screened patients will be eligible for randomization we plan to screen about 400 patients.

We will use an adaptive design in METAPANC. Towards the end of the recruitment period, we will conduct a sample size review verifying planning assumptions such as the overall event and dropout rate, i.e. based on non-comparative data (also referred to as blinded sample size re-estimation); the randomization code will be kept confidential and not be used in the sample size review. Furthermore, a futility analysis will be carried out; futility criteria will be based on the overall event rate and recruitment considerations.

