## Abbreviations

5-FU: 5-fluorouracil
ADR: Adverse drug reaction
AE: Adverse event
ACT, ATC: Anatomical Therapeutic Chemical (Classification System)
alpha-SMA: Alpha Smooth muscle actin
AWMF: Association of the Scientific Medical Societies in Germany (Arbeitsgemeinschaft der Wissenschaftlichen Medizinischen Fachgesellschaften)
BRCA1/2: Breast Cancer Gene 1/2
CA 125: Cancer antigen 125
CA19-9: Carbohydrate Antigen 19 − 9
CD3: Cluster of Differentiation 3
CD4: Cluster of Differentiation 4
CD8: Cluster of Differentiation 8
CHA: Common hepatic artery
CRA: Clinical research associate
CR: Complete remission
CSPAC: Chinese Study Group for Pancreatic Cancer
CTR: Clinical Trials Regulation
CT: Computer Tomography
CTIS: Clinical Trials Information System
CTU UMG: Clinical trials unit University Medicine Göttingen
DPCG: Dutch Pancreatic Cancer Group
DNAseq: DNA sequencing
ECOG: Eastern Cooperative Oncology Group (ECOG Performance Status Scale)
eCRF: Electronic Case Report Form
EORTC: European Organisation For Research And Treatment Of Cancer
EORTC QLQ-C30: EORTC Core Quality of Life questionnaire
EORTC QLQ-PAN26: EORTC health-related quality of life for people with pancreatic ductal adenocarcinoma
FAP: Fibroblast activation protein
GATA6: GATA binding protein 6
GCP: Good Clinical Practice
G-CSF: Granulocyte colony stimulating factor
ICH: International Council for Harmonisation of Technical Requirements for Pharmaceuticals for Human Use
IMP: Investigational Medicinal Product
ITT: Intention-to-treat
KI67: Marker of proliferation Kiel 67
KRAS gene: Kirsten rat sarcoma virus proto-oncogene
MedDRA: Medical Dictionary for Regulatory Activities
mFOLFIRINOX: Modified FOLFIRINOX
ML: Machine Learning
MRI: Magnetic Resonance Imaging
NCCN: National Comprehensive Cancer Network
NCI CTCAE: National Cancer Institute Common Terminology Criteria for Adverse Events
NGS: Next generation sequencing
NYHA: New York Heart Association (NYHA Functional Classification)
OS: Overall survival
PBMC: Peripheral Blood Mononuclear Cell
PD: Progressive disease
PDAC: Pancreatic ductal adenocarcinoma
PFS: Progression-free survival
PR: Partial response
PV: Portal vein
Q-TWIST: Quality-adjusted time without symptoms or toxicity
RECIST v1.1: Response Evaluation Criteria in Solid Tumors version 1.1
RNAseq: RNA sequencing
SAE: Severe adverse event
SD: Stable disease
SDV: Source Data Verification
SMA: Superior mesenteric artery
SmPC: Summary of product characteristics
SMV: Superior mesenteric vein

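### The protocol assigns a mixed model for repeated measures to Q-TWIST, which is a weighted duration with no visit-by-visit score

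*Protocol article*

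**What the plan says.** In the protocol article, Efficacy, one sentence fixes the method for all quality-of-life outcomes: "Quality of life (EORTC QLQ-C30, PAN-26, CIPN20, Q-TWIST) and continuous outcomes assessed repeatedly will be analysed using the so-called Mixed Model Repeated Measures" approach. The next sentence fixes the effect measure: "Treatment differences will be reported as least square means with 95% confidence intervals".

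The Endpoints section places Q-TWIST among the secondary endpoints, as part of "quality of life (EORTC QLQ-C30, PAN-26, Q-TWIST) and translational endpoints". Table 1 lists it there too. The abbreviation list defines it: "Q-TWIST: Quality-adjusted time without symptoms or toxicity".

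The article names no other analysis for Q-TWIST. The Safety section leaves further statistical detail to an analysis plan that is to be final before recruitment ends.

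**The concern.** A mixed model for repeated measures needs one outcome value per patient per visit. It estimates the mean at each visit, and the treatment effect is a difference between those means. QLQ-C30, PAN-26 and CIPN20 supply such values. Q-TWIST does not. It divides survival up to a horizon into time with toxicity, time free of symptoms and toxicity, and time after relapse. It weights the first and last by utilities and adds the three. The result is a number of months for each arm, and the component times are subject to censoring.

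An analysis plan that follows the article inherits a model that cannot be fitted to this endpoint. One that departs from it contradicts the published protocol. Health-related quality of life is a stated secondary objective, and Q-TWIST is the only listed quality-of-life endpoint that combines length of life with its quality. An analysis improvised later would leave the horizon, utilities and state definitions open to choice after the data are known.

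**Working it through.** **1. Setting the passages side by side**

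| Feature | What the stated method needs | What Q-TWIST supplies |
|---|---|---|
| Response | A value at each visit | One summary over a horizon |
| Unit | Score | Time |
| Incomplete data | Missing visits | Censored state durations |
| Effect measure | Difference in least square means | Difference in utility-weighted restricted mean times |

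The phrase about repeated assessment does not exclude Q-TWIST, because Q-TWIST is named in the list. The preceding rule, that time-to-event secondary endpoints are analysed like the primary one, does not help either: a Cox hazard ratio is not a comparison of quality-adjusted time.

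**2. Reproducing the planning figures**

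Inputs (Sample size calculation): two-year survival 15% and 30%, 109 per group, 90% power, two-sided 5%, 5 years of recruitment, at least 2 years of follow-up. Exponential survival is assumed.

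- Hazard ratio: ln(0.30)/ln(0.15) = 0.635, as stated.
- Yearly hazards: λ = −ln(S)/2, giving 0.949 (control) and 0.602 (experimental).
- Events (Schoenfeld): 204.
- Event probability, 1 − (e^(−2λ) − e^(−7λ))/(5λ): 0.969 and 0.905, mean 0.937.
- Patients per group: 204/0.937/2 = 108.9, so 109, as stated.
- Dropout: 218/0.8 = 272.5, against 272 stated.

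The survival assumptions are therefore read as the sponsor meant them.

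**3. The scale on which Q-TWIST lives**

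The three state times add up to restricted mean survival, (1 − S)/λ. To 24 months from randomisation:

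- Control: 0.85/0.949 = 0.896 years, about 10.8 months.
- Experimental: 0.70/0.602 = 1.163 years, about 14.0 months.
- Difference: about 3.2 months.

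That is the Q-TWIST difference if both utilities are set to 1. At lower utilities it depends on time spent in toxicity and relapse, which the article does not give. The estimand is thus a difference in months that varies with the utilities.

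**4. Projected deaths, for the caution on questionnaires**

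Share dead at time t = 1 − e^(−λt):

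| Month | Control | Experimental |
|---|---|---|
| 6 | 38% | 26% |
| 12 | 61% | 45% |
| 24 | 85% | 70% |

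Of 136 per arm, 136 × 0.15 ≈ 20 and 136 × 0.30 ≈ 41 would be alive at month 24, before any dropout.

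**The case against.** **The analysis plan may settle this.** It is not shown, and the article defers details to it. That would answer an omission, but here the method is stated. What stands is that one cannot say the trial has no valid analysis of Q-TWIST, only that the published one does not fit.

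**A least square mean is not impossible.** With two years of follow-up for everyone, a per-patient weighted time up to 24 months could be computed and compared in a linear model. But there would be one value per patient, hence no repeated measures. The plan also allows for about 20% discontinuing the study (272 × 0.20 ≈ 54 patients), whose state times could be censored and need a method that handles this.

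**The authors may have meant the questionnaires that accompany a Q-TWIST analysis.** That is plausible, but it is not what the sentence says.

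**A stronger reading.** A reader might infer that the mixed model is also wrong for the questionnaires, because 70% to 85% of them would be missing through death. The documents do not support this. Those figures are the projected share of patients dead at month 24. The share of all questionnaires lost to death up to then would be lower: about 59–65% (control) and 45–50% (experimental) if forms were due every 2 to 6 months, a schedule that is assumed because the article gives none. The article names no month-24 quality-of-life contrast. The model is a usual choice for these instruments, and the handling of death is commonly left to the analysis plan.

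**Conclusion.** The point holds for Q-TWIST: the stated model and effect measure do not fit an endpoint that the article itself defines as a time, and no alternative is given. This rests on the text and on the standard construction of Q-TWIST, not on any assumed figure. Its reach is one secondary endpoint.

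For the questionnaires there is a caution and no error. The model implicitly carries scores beyond death, and death is expected to be frequent and to differ between arms. The size of any resulting distortion cannot be derived from the documents. The mortality projections rest on the planned two-year survival; the values before month 24 and the 3.2-month figure also assume exponential survival.

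**What to change.** 1. Remove Q-TWIST from the mixed-model sentence in the Efficacy section. Keep QLQ-C30, PAN-26 and CIPN20 there.
2. Add a sentence giving Q-TWIST its own partitioned-survival analysis: restricted mean time in each health state from randomisation to a pre-set horizon (for example 24 months, the minimum follow-up), utility weights, a bootstrap 95% confidence interval for the arm difference, and a threshold plot with both utilities running from 0 to 1.
3. Define the states, utilities and horizon in the analysis plan before it is finalised.
4. As a reporting measure, show the proportion alive in each arm beside late questionnaire contrasts.

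The cost is protocol and analysis-plan wording and some programming. The primary analysis and the sample size do not change. The trade-off is that Q-TWIST will be reported over a range of utilities and not as a single model contrast.

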#### Safety

Standard reporting for adverse events (AEs) and serious adverse events (SAEs). AEs and SAEs will be summarized by frequencies and percentage for each treatment group. AEs will be coded according to MedDRA, analyzed, and presented following ICH E3 Structure and Content of Clinical Study Reports. Events of special interest (e.g. toxicities, post-operative complications) will be analyzed accounting for varying follow-up times and competing events [7].

All details of the statistical analysis including definitions of the analysis sets will be specified in a statistical analysis plan, which will be finalized prior to end of recruitment.

### Assessment of severity/intensity

For the grading of the severity/intensity of an adverse event (AE), the National Cancer Institute Common Toxicity Criteria for Adverse Events (NCI CTCAE) version 5.0 must be used. Medical and scientific judgment should be exercised in deciding whether expedited reporting is appropriate in other situations, such as important medical events that may not be immediately lifethreatening or result in death or hospitalization but may jeopardize the patient or may require an intervention to prevent one of the outcomes listed in the definition above. These events should also usually be considered serious (SAE). All noxious and unintended responses to a medicinal product related to any dose should be considered adverse drug reactions (ADRs). The investigator must report the outcome of AEs and SAEs. All SAEs that have not resolved by the end of treatment visit or discontinuation of IMP treatment, whichever is later, must be followed until the outcome is recovered, recovered with squeal, unchanged/not recovered until death (death due to another cause) or death (due to the SAE). Investigators must report all SAEs immediately within 24 h of knowledge of the event.

### Regulatory, ethical, legal and trial oversight considerations

METAPANC is a phase III clinical trial implemented and reported in accordance with the CTR (EU) 536/2014, ICH-GCP, with applicable Member states regulations, and with the ethical principles laid down in the Declaration of Helsinki. It was submitted, evaluated, and approved via CTIS with Germany as the reporting member state. It is registered under its EU Clinical Trial Number 2023-503558-10-00 in the EU Clinical Trial Register.

### Informed consent

Before enrolment in the clinical trial, the patient will be informed that participation in the clinical trial is voluntary and that he/she may withdraw from the clinical trial at any time without having to give reasons and without penalty or loss of benefits to which the patient is otherwise entitled. The treating physician will provide the patient with information about the treatment methods to be compared and the possible risks involved. At the same time, the nature, significance, implications, expected benefits and potential risks of the clinical trial and alternative treatment will be explained to the patient. During the informed consent discussion, the patient, if applicable, will also be informed about the insurance cover that exists and the insured’s obligations. The patient will be given ample time and opportunity to obtain answers to any open questions. All questions relating to the clinical trial should be answered to the satisfaction of the patient and/or his/her legal representative. In addition, the patient will be given a patient information sheet which contains all the important information in writing.

### Monitoring

In German sites, monitoring is performed by the CRAs of the CTU UMG. Risk-based monitoring will be done according to ICH-GCP E6 and standard operating procedures (SOP) to verify that patients’ rights and wellbeing are protected, reported trial data are accurate, complete and verifiable from source documents and that the trial is conducted in compliance with the currently approved protocol/amendment. All investigators will accept monitoring visits before, during and after the clinical trial to ensure that the trial is conducted, recorded and reported according to the trial protocol, SOPs, ICH-GCP and the applicable regulatory requirements. Prior to the trial, a site initiation visit at each site is conducted in order to train and introduce the investigators and their staff to the trial protocol, essential documents, handling of IMP and related trial specific procedures, ICH-GCP and national/local regulatory requirements. During the trial, the CRA will visit the site regularly depending on the recruitment rate and quality of data. During these on-site visits, the CRA verifies that the trial is conducted according to the trial protocol, trial specific procedures, ICH-GCP and national/local regulatory requirements. The presence of signed informed consents, eligibility of patients, primary endpoint, handling of IMP and documentation/reporting of safety data (e.g. AE/SAE) will be verified by the CRA. The CRA performs also source data verification to ensure that the clinical trial data which are recorded in the source data and eCRFs are complete and accurate. Extent of source data verification and monitor visit frequency will be adapted for individual sites in case of lack of data quality or a high number of protocol violations. All trial specific monitoring procedures, monitoring visit frequency and extent of SDV will be predefined in a trial specific monitoring manual. The investigator must maintain source documents for each patient in the trial, consisting of case and visit notes (hospital or clinic medical records) containing demographic and medical information, laboratory data, electrocardiograms, and the results of any other tests or assessments. All information recorded on eCRFs must be traceable to source documents in the patient’s file. The investigator must also keep the original signed informed consent form (a signed copy is given to the patient). The investigator must give the CRA access to all relevant source documents to confirm their consistency with the eCRF entries.

### Translational research program

The translational research program aims to identify biomarkers for better identification of a potential target population which may benefit from intensified multimodal treatment strategies, to identify molecular biomarkers associated with progression or resistance to study treatment and to identify biomarkers adding to the understanding of PDAC tumor biology. The program will focus on collecting high-quality tissue and liquid biopsy samples, fecal samples and imaging data.

### Exploratory biospecimen analyses

Tissue analyses: samples will be collected and undergo careful pathological quality assessment for subsequent molecular analysis using DNAseq (NGS panel to analyze the mutational status of KRAS, BRCA1/2 and other genes relevant in PDAC pathobiology), RNAseq (to perform signaling pathway analysis, deconvolution of cell lineages and gene expression analysis) and spatial immune profiling (multiplex-Immunofluorescence for tumor and immune markers including tumor markers (cytokeratins, GATA6), fibroblast markers (e.g. alpha-SMA, FAP), immune markers (e.g. CD3, CD4, CD8, Granzyme B) and markers assessing proliferation (KI67) and cell death (e.g. cleaved caspase 3).

Liquid biopsy: collected blood samples will be used to isolate plasma and PBMCs. Quality assessment will be performed, and cell-free DNA and RNA will be isolated for analysis of predictors of response, resistance or toxicity.

Fecal samples: identify biomarkers in the gut microbiome and other biomarkers (e.g. pancreatic enzymes) that are predictive of response to study interventions.

Biological samples drawn during the course of the trial will be collected from the investigator sites and stored and further analyzed by a sponsor assigned central laboratory (West German Biobank and Bridge Institute of experimental Tumor Therapy, West German Cancer Center, University Hospital Essen). Detailed instructions on sample collection, processing, handling and shipment are provided in the laboratory manual (Supplementary Information, Additional file 1).

### Imaging analysis

The development of image-based biomarkers for therapy response prediction and disease outcome presents another exploratory endpoint. For this purpose, baseline and follow up imaging data will be collected for a central review process. Existing and newly developed machine learning (ML) algorithms will be applied to identify PDAC subtypes and predictive therapy response patterns as previously described.

The imaging biomarker translational program includes: secure imaging data transfer and central storage of imaging data, retrospective central image reading and longitudinal imaging data registration, quantitative imaging biomarker extraction (e.g. tumor / metastases, body composition and comorbidities) and ML-based outcome prediction including various clinical endpoints (e.g. therapy response, molecular marker, outcome).

## Discussion

Patients with oligometastatic PDAC and relatively favorable tumor biology may benefit from simultaneous resection of both the primary tumor and liver metastases. This approach could potentially offer a chance for cure or, at least, lead to a survival benefit compared to conventional palliative chemotherapy in selected patients. However, once distant metastases are detected, tumor resection is still not recommended according to German and NCCN guidelines [8, 9], but resection may be considered in selected patients with oligometastases as part of a multimodal treatment approach within the context of clinical trials.

There are no published results from randomized controlled trials on the topic of primary tumor resection in oligometastatic pancreatic cancer. The few systematic reviews consider relatively small case series. The survival prognosis is significantly better in oligometastasis with synchronous resection of the primary tumor and metastases compared to diffuse metastasis [10–12]. Overall, the predominantly retrospective studies provide evidence that overall survival in selected patients with oligometastatic PDAC could be significantly prolonged by primary synchronous resection of both the primary tumor and metastases, compared to patients who are only offered exploration or palliative bypass with chemotherapy [13, 14]. In the multicentre analysis by Tachezy et al., patients who underwent resection of an M1 pancreatic carcinoma showed a significantly longer survival compared to patients who only underwent exploration: 14 months vs. 8 months, but this applies only to the subgroup of patients with pancreatic head carcinoma [15]. These data, however, do not differ significantly from those achieved in the metastatic stage through systemic chemotherapy. In another study, patients with a body/tail pancreatic carcinoma benefited most from a synchronous resection of the primary tumor and liver metastases. A systematic review reports that patients with simultaneous resection of the primary tumor and liver metastases may even have comparable survival rates to patients who underwent resection without distant metastases. These findings are also observed in more recent, small, non-randomized pilot studies, where the tumor marker CA 125 is considered to play a special role as a resection criterion for liver metastases, and a notable degree of patient selection is apparent [16, 17]. The results after neoadjuvant chemotherapy may be more conclusive [11, 18]. In General, data from controlled and randomized studies are missing. In summary, there is evidence suggesting that synchronous resection of the primary tumor and metastases in oligometastatic pancreatic ductal adenocarcinoma, particularly as part of a multimodal treatment strategy, leads to better overall survival outcomes compared to diffuse metastatic pancreatic cancer. How these results compare to a state-of-the-art systemic therapy without resection must be determined by prospective, randomized studies. Until then, resection of the primary tumor and metastases is not yet a clinical standard, even in oligometastatic cases [19].

In the palliative setting, chemotherapy regimens such as FOLFIRINOX or gemcitabine/nab-paclitaxel have recently been established, demonstrating a significant improvement in overall survival (OS), with medians of 11 and 8.5 months, respectively, compared to 7 or 6.7 months with gemcitabine monotherapy [1, 20].

Multimodal treatment strategies, including local therapies, are recommended to enhance disease control and clinical outcomes in these patients. Distinct clinical courses of oligo- and polymetastasis are observed in tumors of different origins, and a comprehensive approach involving multiple entities is required to identify common underlying mechanisms. In pancreatic cancer, the concept of oligometastasis has not yet been established in clinical practice. Furthermore, it is currently unclear whether true oligometastatic disease exists in pancreatic cancer, as it does in colorectal cancer at known stages. The challenge right now is how to select patients who potentially profite from multimodal surgery treatment. Thus finding a strategy to select patient groups who most likely benefit from additional surgery is urgently needed. In this context the METAPANC trial aims to evaluate the effectiveness of multimodal therapy in patients with the clinical presentation of oligometastasis in pancreatic cancer. The combination of highly effective polychemotherapy (mFOLFIRINOX) followed by complete tumor resection is intended to support the potential for curative treatment in these patients — a group that has previously been considered exclusively palliative. The primary objective of this randomized phase III study is to demonstrate the efficacy of this therapeutic concept in terms of overall survival.

METAPANC is currently the only prospective, randomized, controlled, multicentre, phase III trial for curatively intended surgical therapy of oligometastatic pancreatic cancer in Western Europe and the Anglo-American world. In the Asian region, the CSPAC-1 study is currently being conducted as another prospective randomized study in China [4]. As a Phase II study on multimodal therapy for hepatically metastasized pancreatic adenocarcinoma, the HOLIPANC study investigates, in a single-arm study design, the effectiveness and quality of life of a neoadjuvant chemotherapy regimen consisting of liposomal irinotecan combined with oxaliplatin and 5-fluorouracil. The study also evaluates the significance of a curatively intended resection of the primary tumor and oligometastases (up to a maximum of 5 liver metastases).

The multimodal surgical therapy of patients with oligometastatic pancreatic cancer could significantly extend the survival of this patient group within the framework of the METAPANC trial. In order to recommend this treatment regimen outside of clinical trials, data from randomized controlled studies are needed first. An exploratory translational research program is implemented to identify patient groups that could benefit from multimodal surgical therapy. In Germany 26 institutions are currently planned as participating centres (Supplementary Information, Additional file 2). Additionally, international high-volume centres from the Netherlands, Finland, Sweden, and Norway are in preparation. The recruitment of patients has already started. The METAPANC trial is expected to run for at least seven years.

